## Protocol

### Selection of participants

A total number of 90 participants will be recruited for the study on the overlap between stress and alcohol. The Sweden population in 2019 (National Institute of Statistics of Sweden) is approximately 10 million, the population between 18 and 65 years old is less than 5 million
^
1
^. In order to have a significant sample and using one of the most common calculus
^
2
^ to calculate samples with 5M of population, error of 10% and a confidence level of 95 % the sample size must be at least 45 users. Here in this study, two age groups are selected as a result a portion of the population is dropped. The sample size for the test will be 100 users and a 10% more taking into account possible drop offs. However, for stress and alcohol test we are going have 45 subject each as
3 and
4 consider 20 to 30 subjects for statistical significance.

The selection will be made from a larger number of people who will be asked to fill out a questionnaire, and who will also be interviewed to establish their qualifications to be enrolled as participants. The related information sheet, consent form and questionnaire are provided as
*Extended data*
^
16
^.

Each recruited participant will be called to the test site on two occasions, once for stress-related tests and once for alcohol-related tests. The test subjects are divided into two age groups: young (18 – 25 years) and elderly (50 – 70 years) as these age groups have variation in the performance according to the recent research. Sametime, it was also observed that the age between 25 and 49 are often stable in their driving performance. Participants for the stress test will receive a gift card of worth 1500 SEK as gratification for successfully completing all stages of the test. For alcohol test participants the amount of gratification is 2000 SEK.
Table 2 and
Table 3 demonstrate the approximate number of participants from different age groups and road user types, respectively.

**Table 2. T2:** Number of subjects from different age groups.

Tests	Young adult	Elderly	Total
*Alcohol*	20	25	45
*Stress*	20	25	45
**Total**	40	50	90

**Table 3. T3:** Number of participants from different road user types.

Actors	Young adult	Elderly	Total
*Car drivers*	5	7	12
*Motorcyclists*	5	6	11
*Cyclists*	5	6	11
*Pedestrians*	5	6	11
**Total**	20	25	45

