### Design and procedure

One test leader, [name] from MDH, will be assigned to the management of the stress-related tests and [name] from Senseair will be assigned to manage the alcohol-related tests. The detailed description of different test scenarios and procedures are described in the following sections.

**
*Stress test*.** The stress test will be performed as a within-participant design. To induce stress during this part while driving, the participants will be asked to perform other specific tasks where a continuous increase of cognitive load will be required. To keep cognitive loads increasing during the performance, two tasks relevant for the purpose have been selected: time pressure and social stress. During the scenarios, three levels of stress will be induced to the participants. These levels are numbered as 0, 1 and 2. Stress condition with level 0 will be considered as the baseline. Consequently, levels 1 and 2 will be considered as low and high stress, respectively. The low stress condition will include time pressure and the high stress condition will include time pressure and social pressure. Moreover, the participants will drive on three kinds of road (driving condition) and a limited number of events and hazards will occur, allowing study of the drivers’ risk perception and behaviour when coping with unexpected risky events under increased cognitive load conditions. For bicyclists there will be only two types of driving condition. From the total number of participants, approximately 12 will be taking part in this test and they will be divided into three groups to randomize the sequence of stress-eliciting factor insertion during driving or riding a motorcycle in the simulation. For cyclists there will be only two subject groups containing approximately 22 participants each. Description of scenarios and the randomized sequence of scenarios in simulators for different actors are given in the subsequent sections below.
Table 4 illustrates the sequence of induction of stress to participants for 32 minutes of simulator participation. The time for simulator usage will differ for different actor groups. For cyclists, scenario S0.3 and S1.3c will be replaced by similar scenarios defined below. The notations for different scenarios in
Table 4 are further defined in the subsequent sections for different actor groups.

**Table 4. T4:** Test order for the different actors for stress.

Time	4	4	4	4	4	4	4	4	Total

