**SG – 1** **DC – 1**	S1.0 + S2.0 (BL)	S1.1 (LS)	S1.1 (LS) + E1.a	S1.1 (LS) + E1.b	S1.0 + S2.0 (BL)	S1.1 + S2.1 (HS)	S1.1 + S2.1 (HS) + E1.b	S1.1 + S2.1 (HS) + E1.c	**32** **mins**
**SG – 2** **DC – 2**	S1.0 + S2.0 (BL)	S1.1 (LS)	S1.1 (LS) + E2.a	S1.1 (LS) + E2.b	S1.0 + S2.0 (BL)	S1.1 + S2.1 (HS)	S1.1 + S2.1 (HS) + E2.b	S1.1 + S2.1 (HS) + E2.c	
**SG – 3** **DC – 3**	S1.0 + S2.0 (BL)	S1.1 (LS)	S1.1 (LS) + E3.a	S1.1 (LS) + E3.b	S1.0 + S2.0 (BL)	S1.1 + S2.1 (HS)	S1.1 + S2.1 (HS) + E3.b	S1.1 + S2.1 (HS) + E3.c	

SG: subject group, DC: driving condition, BL: baseline, LS: low stress, HS: high stress.

During the experiments, two participants from each actor group will be tested in the simulator each day. Each of the participants will be clearly briefed about the task and their responsibilities. Afterwards, physiological equipment will be attached to their body. Each participant will require around 2.5 hours to prepare fully for the tests. They will participate for about 40 minutes including some practice. After the test finishes, they will be debriefed, and the equipment will be removed.
Table 5 shows the time plan of a test day for participants (car drivers, motorcyclists and cyclists).

**Table 5. T5:** Schedule of a test day for participants in stress test.

Time	Test events

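### If Table 4's one-road-per-group layout stands, dividing car drivers and motorcyclists into groups of about four with no stated age balance can substantially confound road with age

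*Protocol article*

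**What the plan says.** Under Design and procedure (Stress test), the protocol article calls the stress test a within-participant design, has about 12 people taking part, and says that "they will be divided into three groups to randomize the sequence of stress-eliciting factor insertion during driving or riding a motorcycle in the simulation". The stated purpose of the groups is thus to randomize the order in which stress is introduced. For cyclists it gives a different structure: "For cyclists there will be only two subject groups containing approximately 22 participants each".

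Table 4 has one row per subject group. Group 1 is paired with driving condition 1, group 2 with condition 2 and group 3 with condition 3. The order of baseline, low stress and high stress is the same in all three rows; only the road and its road-specific events differ. The text before the table says, however, that participants will drive on three kinds of road.

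On age, Selection of participants says that the young and elderly groups were chosen "as these age groups have variation in the performance according to the recent research". Table 3 gives the age split for each road-user type. Data/statistical analysis treats road as a factor to control and as part of a stress, road and situational-risk interaction; age does not appear in that model. Research question i under Study objective asks how road conditions affect behaviour. The article does not say how people are assigned to subject groups.

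**The concern.** If each group drives one road, the division into groups decides who drives which road. The order of stress levels, which the division is meant to randomize, does not vary between groups. A comparison of roads is then a comparison of different people, about four on each side, drawn from two age groups that the article itself expects to perform differently. Unless age is balanced when the groups are formed, chance alone can put most of the young drivers on one road.

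The answer to the road part of research question i would then carry part of the young-elderly difference. So would any difference in the stress effect between roads, if the two age groups respond differently to stress.

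**Working it through.** **Inputs**
- Car drivers (Table 3): 5 young + 7 elderly = 12, which reproduces the article's figure of about 12. In three groups, 12/3 = 4 each.
- Motorcyclists (Table 3): 5 + 6 = 11, so groups of 4/4/3.
- Cyclists (Table 3): 5 + 6 = 11, so two groups of 6/5. The text's two groups of about 22 make 44, which does not fit 11 cyclists.
- Allocation method: not stated. Simple random division is my assumption.

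**Step 1: one road per person, or three?** A Table 4 row lasts 8 × 4 = 32 minutes, so three rows would take 3 × 32 = 96 minutes. The article allows about 40 minutes including practice, and Table 5 allots 60 minutes (10:30 to 11:30) to simulator plus practice. Only one row fits either figure. The time plan therefore supports reading Table 4 as one road per group, although the sentence about three kinds of road remains in conflict.

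**Step 2: chance imbalance, car drivers.** The 5 young can occupy the 12 places in C(12,5) = 792 ways.

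| Young per road | Placements | Share | Largest gap in share young |
|---|---|---|---|
| 2/2/1 | 3 × 6 × 6 × 4 = 432 | 54.5% | 25 points |
| 3/1/1 | 3 × 4 × 4 × 4 = 192 | 24.2% | 50 points |
| 3/2/0 | 6 × 4 × 6 × 1 = 144 | 18.2% | 75 points |
| 4/1/0 | 6 × 1 × 4 × 1 = 24 | 3.0% | 100 points |

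- Gap of at least 50 points between some pair of roads: (192 + 144 + 24)/792 = 360/792 = 45.5%.
- A road with no young driver: (144 + 24)/792 = 168/792 = 21.2%.
- For one pair of roads named in advance, a gap of at least 50 points: (128 + 96 + 16)/792 = 240/792 = 30.3%.

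**Step 3: effect on a road contrast.** Let D be the mean young-elderly difference in an outcome. With additive effects, the unadjusted contrast between two roads is shifted by (gap in share young) × D:
- best case, 2 v 1: (0.50 − 0.25) × D = 0.25 D
- 3 v 1: (0.75 − 0.25) × D = 0.50 D
- 3 v 0: (0.75 − 0) × D = 0.75 D

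The article gives no value for D, so this cannot be put in outcome units.

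**Step 4: can age be adjusted for afterwards?** With one summary value per driver, the variance of an age-adjusted road contrast is σ²[1/4 + 1/4 + gap²/W], where W is the sum over roads of a(4 − a)/4 and a is the number of young on that road.
- 2/2/1: W = 1 + 1 + 0.75 = 2.75. For 2 v 1: 0.5 + 0.0625/2.75 = 0.523, or 5% above 0.5.
- 3/1/1: W = 0.75 × 3 = 2.25. For 3 v 1: 0.5 + 0.25/2.25 = 0.611, or 22% above.
- 3/2/0: W = 0.75 + 1 + 0 = 1.75. For 3 v 0: 0.5 + 0.5625/1.75 = 0.821, or 64% above.
- 4/1/0: W = 0 + 0.75 + 0 = 0.75. For 4 v 0: 0.5 + 1/0.75 = 1.833, or 267% above.

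An additive age term can always be fitted, because 5 young cannot fill whole groups of four and so at least one road is always mixed. The price rises steeply with the imbalance.

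**Step 5: other road users.** There are C(11,5) = 462 placements.
- Motorcyclists in 4/4/3: gap of at least 50 points in 210/462 = 45.5%; at least one road with a single age group in 114/462 = 24.7%.
- Cyclists in 6/5: gap of at least 50 points in 37/462 = 8.0%.
- The motorcyclist scenario list names only two driving conditions but also gives highway events. If there are only two roads, the 6/5 figure of 8.0% applies to motorcyclists too.

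**Step 6: after dividing within age group.** Cars are always 2/2/1 young and 2/2/3 elderly. The largest gap is fixed at 25 points; the 45.5% and the 21.2% both become 0%.

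**The case against.** The strongest objection is that the point leans on silence. The article names no allocation method, and a journal article commonly leaves the allocation list and its stratification factors to the full protocol. That stands. A reader might infer that the groups are formed without regard to age, but the article neither says so nor says that they are balanced. The percentages describe simple random division, which is an assumption.

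The premise is also contested inside the article. If every participant drives every road, age cannot confound road at all. That stands as a reason to reconcile the two statements first, although the time plan does not leave room for three Table 4 rows.

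A reader might further infer that road contrasts simply turn into age contrasts. The figures do not support that. Complete separation of age between some pair of roads occurs in 3.0% of car divisions, the likeliest split is also the best one, and in 78.8% (100 − 21.2) every road has both age groups. Nor is it right that age and road cannot be disentangled: adjustment is possible, but imprecise.

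Finally, the study is declared exploratory, and its headline stress effect is a within-participant comparison that this imbalance does not bias. That stands too, and limits the point to road contrasts and the stress-by-road interaction. It does not remove the point, since road conditions open research question i and road is in the stated model.

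**Conclusion.** The point holds in a conditional and limited form. As tabulated, road is a between-group factor with about four car drivers or motorcyclists per road; the text can be read otherwise and must be reconciled with Table 4. If road stays between groups, the article describes neither age balancing in the division nor an age term in the model, despite its own statement that age matters for performance.

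Under simple random division, a substantial age imbalance between some pair of roads arises in just under half of divisions for cars, and likewise for motorcyclists if they form three groups; it is uncommon for cyclists. The resulting confounding of road and stress-by-road contrasts is usually partial, and its size in outcome units is unknown because no age effect is given. It is a minor point, worth acting on because the remedy is nearly free.

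**What to change.** First, reconcile Table 4 with the text of Design and procedure: state whether each participant drives one road or all of them, and whether the stress order varies between groups. In the same edit, settle the cyclist group size and the number of motorcyclist roads.

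If road stays between groups, state that subject groups are formed at random separately within each age group and road-user type:
- **Cars:** young 2/2/1 and elderly 2/2/3, with the road that receives the odd number drawn at random.
- **Motorcyclists in three groups:** young 2/2/1 and elderly 2/2/2, with the single young rider in the group of three.
- **Cyclists:** young 3/2 and elderly 3/3.

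Include age group as a term in the road contrasts and in the stress-by-road contrasts, because stratified division still leaves 25 points between roads for cars.

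The cost is a revised allocation list and one model degree of freedom in each contrast; for 12 car drivers on three roads, the residual falls from 12 − 3 = 9 to 8. No extra participants, sessions or measurements are needed, since age is already recorded.

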**Participant 1**	
08:00	Arrival at Senseair
08:10 – 08:20	Primary training
08:20 – 10:00	Preparation of physiological equipment
10:00 – 10:30	Training on levels of stress & scenarios
10:30 – 11:30	Performing in simulator + practice
11:30 – 11:50	Removal of physiological equipment and debriefing
**Participant 2**	
13:00	Arrival at Senseair
13:10 – 13:20	Primary training
13:20 – 15:00	Preparation of physiological equipment
15:00 – 15:30	Training on levels of stress & scenarios
15:30 – 16:30	Performing in simulator + practice
16:30 – 16:50	Removal of physiological equipment and debriefing

For all actor types, time pressure (s1) and social pressure (s2) were always manipulated as a common factor and other factors that are different under each specific actor type:

*Car driver*

Different scenarios to support the levels of stress for car drivers are given below:

Driving condition – kind of road

DC – 1: City roadDC – 2: Country roadDC – 3: Highway

S1 – Time pressure

S1.0 – No time pressureS1.1 – Time pressure

S2 – Social pressure

S2.0 – No social pressureS2.1 – Social pressure

E – Unexpected risky events

E1 – Unexpected risky events on city roadE1.a – Rush hour heavy trafficE1.b – Pedestrian crossing the road without zebra crossingE1.c – Diversion due to construction works

E2 – Unexpected risky events on country roadE2.a – Sudden entry of a car from the side roadE2.b – Motorcyclist riding in front in zigzag fashionE2.c – Sharp turn after an uphill and an oncoming vehicle in the opposite direction

E3 – Unexpected risky events on highwayE3.a – Diversion due to construction worksE3.b – Heavy vehicle entering the highway from acceleration laneE3.c – Low visibility due to fog

*Motorcyclist*

Different scenarios to support the levels of stress for motorcyclists are given below:

Driving condition – kind of road

DC – 1: City roadDC – 2: Country road

S1 – Time pressure

S1.0 – No time pressureS1.1 – Time pressure

S2 – Social pressure

S2.0 – No social pressureS2.1 – Social pressure

E – Unexpected risky events

E1 – unexpected risky events on city roadE1.a – Rush hour heavy trafficE1.b – Pedestrian crossing the road without zebra crossingE1.c – Diversion due to construction works

E2 – Unexpected risky events on country roadE2.a – Sudden entry of a car from the side roadE2.b – Car driving in front in zigzag fashionE2.c – Sharp turn after an uphill and an oncoming vehicle in the opposite direction

E3 – Unexpected risky events on highwayE3.a – Car cutting-in in front of the motorcycleE.3b – Heavy vehicle entering the highway from acceleration laneE.3c – Low visibility due to fog

*Cyclist*

Scenarios to be faced by cyclists in the simulator test for stress are outlined below:

Driving condition – kind of road

DC – 1: City roadDC – 2: Country road

S1 – Time pressure

S1.0 – No time pressureS1.1 – Time pressure

S2 – Social pressure

S2.0 – No social pressureS2.1 – Social pressure

E – Unexpected risky events

E1 – unexpected risky events on city roadE1.a – Rush hour heavy trafficE1.b – Car cutting-in in front of the cycleE1.c – Diversion due to construction works

E2 – Unexpected risky events on country roadE2.a – Sudden entry of a car from the side roadE2.b – Car brushing while passing the bicycleE2.c – Low visibility due to dusk

*Pedestrian*

As the pedestrian simulator tends to easily cause fatigue and nausea, tests will be conducted for limited duration and will include breaks every 5 – 10 minutes. The experiments will be performed using an urban scenario with/without time and social pressure. Moreover, some particular conditions will be simulated while conducting the experiment.

S1 – Time pressure

S1.0 – No time pressureS1.1 – Time pressure

S2 – Social pressure

S2.0 – No social pressureS2.1 – Social pressure

C – Particular conditions

C1 – Construction on the sidewalk (requiring the pedestrian to perform a slalom)C2 – Crowded sidewalk (lots of people moving slowly on the sidewalk)C3 – Prolonged red light at the crosswalk (with road traffic)

Since the pedestrian simulator is the one more likely to cause discomfort, a short break time is reserved as per
Table 6.

**Table 6. T6:** Test order for pedestrians.

Time	2	1.5	1.5	3	15	2	1.5	1.5	3	Total
	S1.0 + S2.0 (BL)	S1.1 (LS)	S1.1 (LS) + C1	S1.1 (LS) + C2	Break	S1.0 + S2.0 (BL)	S1.1 + S2.1 (HS)	S1.1 + S2.1 (HS) + C2	S1.1 + S2.1 (HS) + C3	31 min

BL: baseline, LS: low stress, HS: high stress.

**
*Alcohol test*.** The influence of alcohol consumption on behaviour in the simulator models will be studied in each of the test subjects by first running a test in the sober condition, then consuming alcohol with 0.8 g alcohol/kg body mass. This will normally result in a breath alcohol concentration well above the US legal limit of 0.4 mg/L. A test at this intoxication level is performed in all simulators. Then the participant is allowed to rest until BrAC has declined to 0.3 mg/L, and the test procedure is repeated at this concentration level. The final test run is performed when the subject has reached below 0.1 mg/L. The decline is typically 0.08 ± 0.01 mg/L per hour
^
24
^ and therefore the duration of the entire test is expected to be 6–8 hours in each test subject. A tentative schedule of a test day for participants from all actor groups is given in
Table 7. The exact number of simulator-driving sessions and the finish time will depend on how fast the alcohol concentration is decreasing and for how long the skin electrodes provide adequate electroencephalography (EEG) recordings.

**Table 7. T7:** Schedule of a test day for participants in alcohol test.

Time	Test Events

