**Participant 1**	
08:00	Arrival at Senseair
08:10 – 08:20	Primary training
08:20 – 09:00	Preparation of physiological equipment & practice
09:00 – 09:15	Simulator driving (sober)
09:15 – 09:45	Alcohol consumption
09:45 – 10:20	Wait to allow alcohol affecting the participant
10:20 – 10:30	Simulator driving (with high alcohol effect)
10:30 – 11:00	Wait to allow the change in alcohol level
11:00 – 11:10	Simulator driving (with decreased alcohol effect)
11:10 – 11:40	Wait to allow the change in alcohol level
11:40 – 12:00	Simulator driving (with decreased alcohol effect)
12:00 – 12:30	Wait to allow the change in alcohol level – lunch break
12:30 – 12:40	Simulator driving (with decreased alcohol effect)
12:40 – 13:10	Wait to allow the change in alcohol level
13:10 – 13:20	Simulator driving (with decreased alcohol effect)
13:20 – 16:00	Wait to diminish the effect of alcohol
16:00 – latest	Participant will be driven to his/her residence.

**
*Naturalistic tests in simulators*.** All of the four types of actors will take part in the simulator together to test their behaviour under the influence of stress and alcohol separately in some natural scenarios. An example task for naturalistic driving in the simulator is described below.

*Test scenario 1*

There will be maximum of six participants taking part in the simulator study: one pedestrian, one cyclist, one motorcyclist and three car drivers. Moreover, some AI agents will be present in the simulation. Several streets in the environment will be closed due to some reasons like road or construction works etc. Participants will be participating in the test for around 5 – 10 minutes.
Figure 5 illustrates test scenario 1. Each of the participants from different actor groups will have separate goals –

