### Data management

Along with the data mentioned above, some personal data - date of birth, sex, weight, height, alcohol drinking habits, driver’s license for cars/motorcycles etc. will be recorded.

**
*Documentation of investigation procedures*.** The study is an exploratory investigation using the physiological data i.e., the heart (ECG), variation of heartbeat (HRV), cardiovascular dynamics (BVP), skin response (GSR), the muscles (EMG), respiration (RP), activity in the brain (EEG), and the eyes (EOG). The equipment continuously records data from the moment the simulator study is turned on until it is shut down. However, no intervention will be performed and no data regarding intervention will neither be documented nor stored during the data collection.

The alcohol-related tests will be performed with similar physiological data collection routines. In addition, the subject’s reaction to simulated stimuli will be recorded, for example their steering operation and balancing. This will be done by recording speed, lateral position, break and steering wheel angle. The readings of breath alcohol concentration will be performed before and after each recording session.

Video recordings of test participant face will be made to better understand their behaviour during the driving. The road in front of the vehicle will be resumed. Also, data from the simulator i.e., speed, lateral position, break, steering wheel angle, use of the arrows and the behaviour of other vehicles’ drivers will be analysed. Further, there will be audio recording during data collection.

**
*Data storage and sharing*
**

*General procedures*

The SIMUSAFE project adopts appropriate procedures so as to ensure the necessary confidentiality and respect of privacy by establishing a set of principles and procedures to guide the partners to achieve the goals and objectives of the SIMUSAFE project. Strict accordance with applicable international, EU and national law, especially the EU directive 95/46/EC is guaranteed, and any related updates will be observed.

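### The alcohol test always runs sober first, and the one later run that could expose practice or fatigue, the closing run below 0.1 mg/L, is not secured by the schedule or by the EEG rule

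*Protocol article*

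**What the plan says.** Under Design and procedure, the Alcohol test paragraph fixes one order for everyone: "first running a test in the sober condition, then consuming alcohol". A run at high intoxication follows, then a run at 0.3 mg/L, then a final run below 0.1 mg/L. Table 1 labels the range 0 to 0.1 mg/L as sober. The article gives a decline of 0.08 ± 0.01 mg/L per hour and expects the whole test to take 6 to 8 hours.

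Table 7, described as tentative, lists six drives: sober at 09:00–09:15, high alcohol effect at 10:20–10:30, and four at decreased effect (11:00–11:10, 11:40–12:00, 12:30–12:40 and 13:10–13:20). From 13:20 to 16:00 it lists only a wait.

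The number of sessions is left open. It depends on the speed of the BrAC decline and on "for how long the skin electrodes provide adequate electroencephalography (EEG) recordings".

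The simulator records speed, lateral position, braking and steering. On BrAC, the Data management section says: "The readings of breath alcohol concentration will be performed before and after each recording session". Research question ii, under Study objective, compares behaviour by alcohol level with the accident-risk relation from retrospective work.

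**The concern.** With a single fixed order, any change over the day that is not due to alcohol is credited to alcohol. Improvement after the first drive hides impairment in the intoxicated runs, and fatigue exaggerates it. The alcohol test describes no varied order and no non-drinking comparison.

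A closing run at near-sober BrAC gives a way to see the problem: if the first and last runs differ, order matters. That run is also the one most exposed to loss, because it comes last. If it is not made, no later analysis can recover it, and question ii then rests on a dose-response relation whose reference is always the first drive of the day.

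**Working it through.** **1. The plan's own duration.** Inputs: arrival at 08:00 and first intoxicated run at 10:20 (Table 7), decline of 0.08 mg/L per hour, end point 0.1 mg/L. The BrAC at 10:20 is not given beyond being well above 0.4 mg/L, so 0.4 to 0.6 is assumed, with decline from then on.

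Duration = 2.33 h + (start − 0.1)/0.08.

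- Start 0.40: 2.33 + 3.75 = 6.1 h
- Start 0.50: 2.33 + 5.00 = 7.3 h
- Start 0.55: 2.33 + 5.63 = 8.0 h
- Start 0.60: 2.33 + 6.25 = 8.6 h

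The stated 6 to 8 hours is reproduced for starts of about 0.40 to 0.55.

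**2. BrAC at the last listed run.** From 10:20 to 13:10 is 2.83 h, a fall of 2.83 × 0.08 = 0.23 mg/L.

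- From 0.4: about 0.17 at 13:10 (0.15 to 0.20 for declines of 0.09 to 0.07). It reaches 0.1 after 3.75 h, at about 14:05.
- From 0.5: about 0.27 at 13:10 (0.25 to 0.30). It reaches 0.1 after 5.0 h, at about 15:20.

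Both times fall inside the 13:20–16:00 wait. Even the fastest case (start 0.4, decline 0.09) needs 3.33 h and gets there at about 13:40. The 6 to 8 hours leave room for the closing run, but Table 7 does not list it.

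**3. Order and alcohol cannot be separated as categories.** With the text's four conditions always in the same four positions, a model with condition and position effects has 7 columns and rank 4, whatever the number of participants. In Table 7's post-alcohol runs, BrAC at a constant decline correlates −1.0 with clock time.

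**4. Effect of first-run learning on the BrAC slope.** Suppose performance gains g in every run after the first. The spurious slope is g × (mean BrAC)/Sxx, where Sxx is the sum of squared deviations of BrAC from its mean. The levels 0.5 and 0.08 are assumptions.

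- Runs at 0, 0.5, 0.3, 0.08: mean 0.22, Sxx 0.1528, bias 0.22g/0.1528 = 1.44g per mg/L.
- Last run lost (0, 0.5, 0.3): mean 0.2667, Sxx 0.1267, bias 0.2667g/0.1267 = 2.11g per mg/L.

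For an assumed g of 0.1 SD these are 0.14 and 0.21 SD per mg/L. For 0.2 SD they are 0.29 and 0.42. The result varies with the assumed high level:

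- At 0.4: 0.195g/0.1043 = 1.87g with all four runs, and 0.2333g/0.0867 = 2.69g without the last.
- At 0.6: 0.245g/0.2163 = 1.13g with all four runs, and 0.300g/0.1800 = 1.67g without the last.

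**5. Would a linear run-number term repair it?** For the four runs, the cross-product of BrAC with run number is 0.02, that of the learning step with run number is 1.5g, and the sum of squares of run number is 5. Adjusted bias = (0.22 − 0.02 × 1.5/5)g / (0.1528 − 0.02²/5) = 0.2140g/0.1527 = 1.40g. The term removes about 3% of the bias.

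**6. Would averaging the first and last runs repair it?** The high-versus-sober contrast carries bias g against the first run alone. Against the average it carries g − (0 + g)/2 = g/2. That halves the bias without removing it, and the last run contains some residual alcohol.

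**7. Slot lengths.** Sober 15 min; later 10, 10, 20, 10 and 10 min. The sober slot is longer than four of the five later ones: 1.5 times a 10-minute slot and 0.75 times the 20-minute slot.

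**The case against.** The strongest reply is that a declining-BrAC test within one day cannot be counterbalanced once alcohol has been taken, that the study is declared exploratory, and that the text already plans a near-sober closing run. All three are true. A reader might infer that the design has no later sober reference; the Alcohol test paragraph contradicts that. The point is only that this run is not secured.

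Table 7 is tentative, and the text lets the number of sessions and the finish time follow the BrAC decline. A reader might infer that the closing run has been abandoned; the documents show only that text and table do not agree. Likewise, a reader might take the EEG wording to mean that recorded runs will be deleted. It says only that the number of sessions depends on EEG adequacy, so the risk is of runs not being made.

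Two further inferences go beyond the documents:

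- **Too little practice.** Table 7 gives 40 minutes to equipment and practice together, against 100 minutes for equipment alone in Table 5, but neither states how much practice is given. Primary training comes first, and if the same people attend the stress test beforehand, g would be smaller.
- **Unequal exposure already biases the results.** Nothing says that raw counts per run will be compared. The signals are sampled continuously, so rates and equal windows remain open.

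The exploratory label removes the need for a power analysis. It does not remove the confounding from question ii.

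**Conclusion.** The point stands in a limited form. The fixed order mixes alcohol with practice and fatigue. The final run below 0.1 mg/L is the one planned run able to show this, and two statements in the article leave it exposed: Table 7's last listed drive comes at about 0.17 to 0.27 mg/L for assumed starts of 0.4 to 0.5, and sessions are tied to electrode life although the driving measures and BrAC need no EEG.

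Losing that run raises the slope bias from first-run learning from 1.44g to 2.11g per mg/L and removes the order check altogether. These figures rest on the assumed BrAC levels, a constant decline from 10:20, and a one-step gain g whose size the documents do not give. They show how sensitive the result is; they do not show that a bias of any given size will occur.

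**What to change.** - Reconcile the final run in the Alcohol test text with Table 7. Which timing should stand is for the sponsor to decide.
- State that loss of adequate EEG does not end the driving sessions: driving measures and BrAC are still recorded, and EEG is treated as missing for that run.
- Report the first sober run against the final run below 0.1 mg/L as the order check. Use their average as a sensitivity reference, noting that it halves a first-run learning bias in the high-versus-sober contrast and includes some residual alcohol.
- Compare runs by rates or equal time windows, because the slots differ in length.
- Do not rely on a linear run-number term as the correction, since it leaves the slope bias at 1.40g.

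The cost is a few sentences in the protocol and the analysis wording. Some runs will lack EEG, and some recorded minutes may go unused.
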